## Abstract

**Background:**

There is insufficient evidence on the effectiveness of acupuncture for irritable bowel syndrome (IBS) for conclusions to be drawn. Given the current interest in acupuncture by patients, it is in the public interest to establish more rigorous evidence. Building on the positive findings from a pilot study, in this paper we present the protocol for a fully-powered trial designed to establish whether or not acupuncture is effective and cost-effective.

**Methods/Design:**

In this pragmatic randomised controlled trial we will randomise patients recruited directly from GP databases to either 10 sessions of acupuncture plus usual GP care or to usual GP care alone. The primary clinical outcome will be the IBS Symptom Severity Score (SSS) (maximum score 500) at three months, and at 12 month assessing whether there is an overall benefit. We estimate the sample size required to detect a minimum clinical difference at 90% power and 5% significance to be 188 patients. To allow for loss to follow up we will recruit 220 patients drawn from an estimated primary care population of 140 000. Analysis will be by intention-to-treat, and multiple imputation is to be used for missing data.

In a nested qualitative study using in-depth interviews, we will explore how patients, acupuncturists, and GPs explain and subsequently understand acupuncture to work. We will use purposive sampling to identify patients and flexible topic guides for the interviews. The data analysis will lead to a thematic description of how patients and practitioners explain how acupuncture works, and whether or not the explanations influence treatment outcome and/or referrals.

We will undertake a cost-effectiveness analysis at 12 months by comparing resource use in the two groups with any treatment benefit. We will use the EQ-5D to measure health-related quality of life and convert into quality adjusted life years (QALYs). We will generate cost effectiveness acceptability curves (CEACs) exploring the probability that acupuncture will produce an acceptable cost per QALY at different cost-effectiveness thresholds.

**Discussion:**

The trial has received NHS ethics approval and recruited 233 patients between November 2008 and June 2009. Results are expected in 2011.

**Trial Registration:**

Current Controlled Trials ISRCTN08827905

## Background

Irritable bowel syndrome (IBS) is the most common disorder encountered by gastroenterologists and the most common functional bowel disorder seen by doctors in primary care [1]. The causes of the disorder are unknown but sufferers are said to experience an increased gastrointestinal stress response consistent with an up-regulation in neural processing between the gut and the brain, termed the "brain-gut axis" [2]. Irritable bowel syndrome is thought to be exacerbated by psychosocial stressors, so treatment is most successful when a multi-component, comprehensive approach is used. Therefore usual care involves a number of interventions as options, including pharmaceuticals, psychological interventions and dietary changes. According to a Cochrane review, bulking agents and antidepressants lack a clear benefit in treating IBS, while antispasmodics, as a category, provide relief of abdominal pain [3]. A review of conventional treatments found that they are rarely effective in managing IBS symptoms [4], a finding that is supported by the Cochrane review [3]. Conventional treatments for IBS are associated with risks including adverse events, worsening of symptoms, and financial costs [5]. The direct and indirect costs associated with IBS are potentially considerable [6]. Some patients are satisfied with current therapies, but many others are frustrated, feeling that advice lacks clarity, conflicts with other GPs' advice and may not work [7].

In this context it is not surprising that patients are increasingly turning to complementary and alternative medicine [8]. An estimated 10% of the UK population uses complementary and alternative medicine [9]. Alternative and complementary techniques are used by between 11% and 43% of patients with gastrointestinal disorders [10]. A survey of GPs found that there is an "effectiveness gap" in currently available treatments in primary care for IBS [11]. Among acupuncture patients, 5% state that their primary complaint is gastrointestinal, most commonly IBS [12]. According to a recent Cochrane review of acupuncture for IBS, the studies to date are of poor quality, heterogeneous in terms of interventions, controls and outcomes, and therefore provide insufficient evidence to determine if acupuncture is an effective treatment for IBS [13]. A recent safety survey of patient reports over a three month period found that acupuncture treatments performed by competent practitioners are rarely associated with adverse events [14].

In this study, we used our pilot study (ISRCTN32823720) as a platform to design a full-scale trial of acupuncture in order to provide robust evidence on acupuncture as a potential referral option in primary care. The primary objective is to establish rigorous evidence of the clinical effectiveness and cost-effectiveness of acupuncture plus usual GP care when compared to usual GP care alone for patients with irritable bowel syndrome (IBS) in primary care. The secondary objective is to perform a qualitative exploration of the experience of patients, GPs and acupuncturists in using acupuncture to treat irritable bowel syndrome.

## Methods/Design

We will conduct a parallel-arm randomised controlled trial to determine the effectiveness and cost-effectiveness of acupuncture plus usual care compared to usual care alone for the treatment of IBS. The rationale for this unblinded pragmatic design is that it will best answer practical questions regarding the clinical and cost implications of offering acupuncture as an additional treatment option within primary care [15]. This trial design will not ascertain the extent that 'placebo' effects contribute to the overall outcome. This design will not be able to ascertain the contribution to the overall effect from expectation, belief and other non-specific factors such as time and attention. In pragmatic terms, even if some of the effect of the treatment process is due to "placebo", acupuncture cannot be delivered without it, and therefore as with all complex interventions, the important question is whether the overall effect is worth paying for. For patients the primary objective is an improvement in outcome and the contribution of a placebo effect to that improvement is immaterial. The pragmatic trial design provides a real-world comparison to be made for a cost-effectiveness analysis and is directly relevant to policy and decision-makers.

Nested within the trial is a qualitative analysis designed to explore how patients, acupuncturists, and GPs explain and subsequently understand acupuncture to work. The qualitative aspect of this study is designed using a phenomenological approach. Phenomenology is the study of how people describe and experience phenomena, which in this case is acupuncture [16]. The design fulfils a basic and summative evaluation purpose, in that the study will contribute to general knowledge and determine usefulness [17].

### Participant recruitment criteria

To recruit participants, we will use the 'database' recruitment method as we did for the pilot [18]. Participants will be identified via the databases of GP practices in the NHS North Yorkshire & York Primary Care Trust. Our inclusion criteria are that participants must be aged 18 or older, with a diagnosis of IBS from their GP. We will exclude participants who do not speak English, who score less than 100 on the IBS Symptom Severity Score (SSS) [19], who have a current diagnosis of haemophilia, hepatitis, HIV, or cancer, who have had major gastrointestinal surgery in the previous six months, who are pregnant, who have a history of psychosis or substance abuse, or who are receiving acupuncture at the time. Participants will be assessed for IBS using the Rome III criteria [20]. In our pilot study, based in Birmingham, 32 eligible participants consented to participate from four GP practices that together had a registered list size of 20,300 [18]. For the proposed research, we estimate that 220 participants are needed (see below for sample size justification). To recruit this number, we will need a total primary care list size of approximately 140,000 patients, equivalent to 14 GP practices with an average of 10,000 patients each. We plan to recruit GP practices in geographically contained groups, such that each group of practices is located near a clinic that provides acupuncture from qualified acupuncturists. These groups are likely to be in the larger centres of population in the region. Based on our pilot, we estimate that recruitment will take 12 months.

### Randomisation and blinding

We will randomise participants to receive either a short course of traditional acupuncture plus usual GP care or usual GP care alone, using simple concealed randomisation, the most robust method of avoiding possible selection bias [21]. The randomisation sequence will be computer generated at the University of York by an independent data manager at the York Trials Unit, and concealed from the researcher who will subsequently inform participants of their allocation. For those participants allocated to acupuncture, the selection of an acupuncture practitioner will be made by appointment availability and convenience for the participant. As this is a pragmatic trial, neither participants nor researchers will be blind to treatment allocation. Whilst randomisation eliminates selection bias, there are other sources of bias we need to avoid. To assess the impact of participant preferences, we propose to ask participants at baseline for their treatment preferences [22]. To avoid bias due to attrition, participants in both groups will be followed up carefully. Participants will also be given £5 as an incentive to complete the final follow-up questionnaire (they will receive the incentive whether or not they actually complete the forms) in order to reduce attrition rates. Incentives such as this have been shown to improve follow-up rates [23].

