### Outcome measures

Our primary outcome measure will be the IBS Symptom Severity Score (IBS SSS). This questionnaire is scored from 0 to 500 (< 75 = no IBS, 75-175 = mild case, 175-300 = moderate and 300+ = severe), and has been validated for use in IBS patients [19]. Our secondary outcomes will be the IBS Non-Colonic Symptom Score (which includes lethargy & tiredness, "wind", backache, and other symptoms) [24], the SF-12 to evaluate patients' health related quality of life [25], and the Hospital Anxiety and Depression Scale [26]. The primary outcome for the cost-effectiveness component of the study will be EQ-5D [27]. We will also collect data on medication use, health services used and days lost from work. Along with baseline data, all outcomes will be sought by postal questionnaire at three, six, nine and 12 months, and where this fails, the main outcome measure will be sought by telephone. We will also seek information associated with hospitalisations. Open text questions will be used to gather qualitative data on patient experiences of acupuncture, including adverse events. We will also collect data on safety and treatment processes from log books completed by the acupuncturists. We will use in-depth interviews with flexible topic guides to collect qualitative data.

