### Sample size required

The sample size required for a full-scale trial is based on a minimal clinical difference of 50 points on the primary outcome measure the IBS Symptom Severity Score [19]. A residual standard deviation of 90 points was observed in our pilot [18], and taking into account potential sampling bias [28] by using a one-sided 90% confidence interval for the variance, we estimate an adjusted standard deviation to be 105 points. Using this estimate, the sample size required to detect a difference at 90% power and 5% significance level is 188 patients in a two-arm trial. To allow for loss to follow up, of a similar proportion observed in the pilot, our proposed trial requires 220 patients.

For the nested qualitative study, we will collect data from 30 patients, a sample size that is likely to be sufficient to map the diversity of patients in primary care [29]. We will use purposive sampling guided by a matrix based on gender, intervention, preference, and baseline IBS severity as illustrated below in Table 1.

**Table 1 T1:** Qualitative sampling matrix

Baseline IBS Score	Preferred Acupuncture		Preferred Other		Total	
	Male	Female	Male	Female	Male	Female
**Mild - Moderate**	3-4	3-4	3-4	3-4	**6-8**	**6-8**
**Severe**	3-4	3-4	3-4	3-4	**6-8**	**6-8**
**Total**	**6-8**	**6-8**	**6-8**	**6-8**	**12-16**	**12-16**

We will also collect qualitative data from 10 GPs and 10 acupuncturists using convenience samples of practitioners in North Yorkshire, excluding those involved in the trial. It has been suggested that a sample size of 10 is adequate for phenomenological studies because researchers are seeking common features of experience [30].

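### The blinding statement makes no exception for outcome collectors or analysts, so callers taking the primary score by telephone may know the arm: an avoidable, probably small, source of bias

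*Protocol article*

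**What the plan says.** Four parts of the protocol article bear on this.

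- **Randomisation and blinding** states: "As this is a pragmatic trial, neither participants nor researchers will be blind to treatment allocation". It qualifies this for no role. The only concealment described is that of the randomisation sequence, which is "concealed from the researcher who will subsequently inform participants of their allocation". That protects allocation, not later measurement.
- The same section goes on: "Whilst randomisation eliminates selection bias, there are other sources of bias we need to avoid". The measures it then names are asking for treatment preferences at baseline, careful follow-up of both groups and a £5 incentive with the final questionnaire.
- **Outcome measures** makes the IBS SSS (0 to 500) the primary outcome. Questionnaires go by post at three, six, nine and 12 months, and "where this fails, the main outcome measure will be sought by telephone". The sentence is in the passive and does not say who calls.
- **Methods/Design** gives the reason for open treatment: "The rationale for this unblinded pragmatic design is that it will best answer practical questions regarding the clinical and cost implications". It accepts that expectation, belief, time and attention cannot be separated from the overall effect.

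**The concern.** The reason given is narrower than the rule it is meant to support. Expectation and attention come with acupuncture as it is offered in practice, so counting them in the effect is consistent with a pragmatic question. A caller's influence on the number written down is not part of offering acupuncture. It is measurement error, and being pragmatic does not make it unavoidable. The same holds for the analyst, who can work on coded arms in any design.

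A postal form is completed by the patient alone. On the telephone another person puts the questions and records the answers to a subjective scale. If that person knows the arm, prompting or interpretation may differ between arms. The primary analysis under Data analysis adjusts for baseline score and GP practice, which does not remove such a difference. Multiple imputation deals with scores that are missing, not with scores that were obtained differently. A systematic shift of this kind does not shrink with a larger sample.

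**Working it through.** **Inputs from the article (Sample size required).** The target is "based on a minimal clinical difference of 50 points on the primary outcome measure". For the spread, "we estimate an adjusted standard deviation to be 105 points". Power is 90%, significance 5%, total 188, raised to 220 for loss to follow-up. Two-sided testing and 1:1 allocation are assumed, since neither is stated.

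**The plan's own figure.** A two-sample t-test with a difference of 50 and SD 105 needs 93.65, so 94 per arm and 188 in total. This agrees with the article. (The normal approximation gives 93 per arm, 186 in total.) Also 188/220 = 0.855, an implied loss of 14.5%. No sample size figure is in dispute; these numbers only set the scale.

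**Standard error of the difference.** 105 × √(2/94) = 15.3 points.

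**Inputs not in the documents.** The share of scores taken by telephone and the size of any caller effect are both assumed below.

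**Bias from a caller effect in one arm.** Bias = telephone share in that arm × shift.

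| Telephone share | Shift (points) | Bias (points) | Bias / 50 | Bias / SE | Two-sided type I error |
|---|---|---|---|---|---|
| 10% | 25 | 0.10 × 25 = 2.5 | 5% | 0.16 | 5.3% |
| 15% | 25 | 0.15 × 25 = 3.75 | 7.5% | 0.24 | 5.7% |
| 20% | 25 | 0.20 × 25 = 5.0 | 10% | 0.33 | 6.2% |

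The last column is 1 − Φ(1.96 − bias/SE) + Φ(−1.96 − bias/SE).

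**Wider range.** Shares of 5-25% and shifts of 10-50 points give a bias between 0.05 × 10 = 0.5 and 0.25 × 50 = 12.5 points, with type I error between 5.0% and 12.9%. The upper end requires a caller effect as large as the whole target difference, in one arm only.

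**A shift common to both arms.** Bias = shift × (difference in telephone share). With equal shares it is zero. With assumed shares of 20% and 10% and a 25-point shift it is 25 × (0.20 − 0.10) = 2.5 points. This is an effect of the mode of collection, and blinding the caller does not remove it.

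**The case against.** The case against has several parts.

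- **The caller is not identified.** A reader might infer that staff who know the allocation do take the telephone scores. The article does not say so. It says researchers are not blind and, elsewhere, that scores are sought by telephone; the link is an inference, though a fair one. This stands, and the point is limited to what the text permits.
- **An article condenses a fuller protocol.** Call scripts, a field for mode of collection and sensitivity analyses may be in documents not shown, and their absence here is not an error. This also stands. What is open to criticism is the stated rule: blinded callers or analysts elsewhere would conflict with the sentence as it reads.
- **Some researchers must know the arm.** A reader might conclude that the statement should cover only patients and acupuncturists. The documents do not support that: a researcher tells participants their allocation, and the qualitative sampling is guided partly by intervention. The remedy has to be an exception for particular roles.
- **The avoidable part is small.** The score is reported by patients who know their treatment, mostly by post. Blinding the caller removes only caller influence in the fallback group. It does not touch mode effects or differences in who fails to return the form. This stands and limits the weight of the point.
- **Telephone follow-up is valuable.** It recovers primary outcomes that would otherwise be lost, and the article names attrition as a bias to avoid. Nothing here argues against making the calls.

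**Conclusion.** The concern holds in a limited form. The article leaves researchers unblinded on the ground that the trial is pragmatic, and that ground does not extend to those who take telephone scores or run the analysis. As written, a caller may know the arm when recording the primary outcome.

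The likely size is modest: 2.5-5 points, or 0.16-0.33 standard errors, with type I error of about 5.3-6.2% instead of 5%. This rests on an assumed 10-20% telephone share, an assumed 25-point shift confined to one arm, SD 105 and 94 per arm; the direction is unknown. The illustration concerns the three-month comparison, although the same fallback applies at the later time points.

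A reader might infer that the primary result is seriously compromised. The documents give no telephone share and no caller effect, so they do not support that. This is a cheap improvement, not a flaw that decides the trial.

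**What to change.** - **Wording.** Under Randomisation and blinding, keep the statement for participants, acupuncturists, and the researchers who inform participants of allocation or run the interviews. Add an exception for telephone collectors and for the primary analysis.
- **Calls.** Have telephone scores taken from a fixed script by existing staff who are not told the allocation. That such staff are available is an assumption, because the only trials-unit role the article describes is the data manager who generates the sequence.
- **Analysis.** Run the primary analysis on arm-coded data.
- **Mode.** Record whether each score came by post or telephone, and report a supportive analysis by mode. A postal-only analysis should be read with care: it removes caller influence but drops the late responders, and so brings in selection by non-response.

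**Cost.** Reassigning some staff time, one database field and one additional model run. Some patients will reveal their arm on the call, so blinding will be incomplete. Recruitment ran from November 2008 to June 2009, so calls already made cannot be redone. For those, arm-coded analysis is still possible if the analysis has not been run, and so is the analysis by mode if mode can be recovered from returned forms or call records.

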### Interventions

Acupuncture will be provided by professional acupuncturists who are registered with the British Acupuncture Council, and have at least three years' experience. The acupuncture will be provided at independent clinics that are geographically near the GP practices from which we are recruiting. The participants in this group will be offered up to 10 treatment sessions over a three month period. Acupuncturists will be trained to follow a treatment protocol adapted from the one that was tested by acupuncturists taking part in the pilot trial [18]. The treatment protocol allows sufficient standardisation to assist replication, yet is flexible enough to allow individualised treatments. Adherence to the protocol will be monitored through the use of practitioner logs, which will be collected throughout the trial. In terms of compliance, we expect to obtain similar levels to those achieved in our pilot in which, on average, patients allocated acupuncture took up eight of the ten sessions offered. All patients will remain under the care of their general practitioner and will continue to receive their usual NHS treatment. Both groups will be able seek care elsewhere according to need. We will collect and report information from patients in both groups at three, six, nine and 12 months regarding usual care and treatments they have received.

### Outcome measures

Our primary outcome measure will be the IBS Symptom Severity Score (IBS SSS). This questionnaire is scored from 0 to 500 (< 75 = no IBS, 75-175 = mild case, 175-300 = moderate and 300+ = severe), and has been validated for use in IBS patients [19]. Our secondary outcomes will be the IBS Non-Colonic Symptom Score (which includes lethargy & tiredness, "wind", backache, and other symptoms) [24], the SF-12 to evaluate patients' health related quality of life [25], and the Hospital Anxiety and Depression Scale [26]. The primary outcome for the cost-effectiveness component of the study will be EQ-5D [27]. We will also collect data on medication use, health services used and days lost from work. Along with baseline data, all outcomes will be sought by postal questionnaire at three, six, nine and 12 months, and where this fails, the main outcome measure will be sought by telephone. We will also seek information associated with hospitalisations. Open text questions will be used to gather qualitative data on patient experiences of acupuncture, including adverse events. We will also collect data on safety and treatment processes from log books completed by the acupuncturists. We will use in-depth interviews with flexible topic guides to collect qualitative data.

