### Cost effectiveness

We will undertake a cost-effectiveness analysis at 12 months by comparing resource use in the two groups with any treatment benefit in an incremental cost-effectiveness ratio. The primary analysis will calculate cost-effectiveness from an NHS perspective because of the potential to influence health policy. However, we will also perform cost-effectiveness calculations from a societal perspective to ensure that this research will not be limited in its usefulness. We will collect data from patients and GPs about patients' resource use, such as visits to their GP, visits to other health providers, both within and outside the NHS and medication use, as well as measuring their days off and whether usual activities are affected by their IBS. We will use EQ-5D to measure health-related quality of life and convert into quality adjusted life years (QALYs), in order to calculate an incremental cost effectiveness ratio (cost per QALY gained), after adjusting for baseline EQ-5D score [31]. To measure presenteeism and absenteeism, we will use the Work Productivity and Activity Impairment instrument (WPAI) and convert the scores into a monetary value [32]. We will also use a net monetary benefit approach to generate cost effectiveness acceptability curves (CEACs) exploring the probability that acupuncture will produce an acceptable cost per QALY at different cost-effectiveness thresholds. This approach accounts directly for uncertainty around the estimates of costs and effects, which is particularly important as this trial is powered on the basis of the clinical effectiveness measure (IBS SSS) rather than the economic outcome measure (EQ-5D). If the intervention is found to be not cost-effective at 12 months, then evaluation over a longer time frame may be considered.

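### The named adverse-event sources are all tied to acupuncture, so adverse-event rates drawn from them cannot be compared between arms

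*Protocol article*

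**What the plan says.** Two sentences in the protocol article, both under Outcome measures, name a source for harms. Patients are covered by this one: "Open text questions will be used to gather qualitative data on patient experiences of acupuncture, including adverse events". Practitioners are covered by this one: "We will also collect data on safety and treatment processes from log books completed by the acupuncturists".

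The same section lists other data with no restriction to one arm: "We will also seek information associated with hospitalisations" and "We will also collect data on medication use, health services used and days lost from work". The outcome schedule is common: "all outcomes will be sought by postal questionnaire at three, six, nine and 12 months". Under Interventions, usual care and treatments received are explicitly a two-arm collection: "We will collect and report information from patients in both groups at three, six, nine and 12 months". Cost effectiveness plans on "comparing resource use in the two groups with any treatment benefit in an incremental cost-effectiveness ratio".

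The Background accepts that the comparator carries harms of its own: "Conventional treatments for IBS are associated with risks including adverse events, worsening of symptoms, and financial costs".

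The objectives at the end of the Background cover effectiveness, cost-effectiveness and a qualitative exploration, with none on comparative safety. Data analysis does not list adverse events among the comparisons between groups.

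**The concern.** Usual care continues in both arms, so events arising from usual treatment can occur in either. Adding acupuncture could plausibly lower them (for example through less medication) or add to them. Either change shows up as an event rate only if both arms are asked the same thing in the same way.

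As described, they are not. An acupuncture patient has repeated contact with a practitioner who logs safety, and is asked an open question framed around acupuncture. A usual-care patient has no practitioner log and no described counterpart to the question. The framing matters inside the acupuncture arm too: a patient who attributes a problem to a tablet has little reason to report it under experiences of acupuncture.

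At stake is how a harms table would be read. Events set out by arm from these two sources would show an excess with acupuncture because of how they were collected, and an empty usual-care column could be mistaken for an absence of events.

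**Working it through.** The article gives no adverse-event rate or target difference, so there is no stated figure to reproduce. The check is which sources reach which arm.

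| Source | Section | Acupuncture plus usual care | Usual care alone |
|---|---|---|---|
| Open-text question that includes adverse events | Outcome measures | Yes, framed around acupuncture | No counterpart described |
| Acupuncturists' log books (safety) | Outcome measures | Yes | None can exist without a trial acupuncturist |
| Hospitalisations | Outcome measures | Sought | Sought (no restriction stated) |
| Medication, health services, lost work days | Outcome measures; Cost effectiveness | Sought | Sought (no restriction stated) |
| Usual care and treatments received | Interventions | Sought | Sought (both groups named) |
| IBS SSS, Non-Colonic Symptom Score, SF-12, HADS, EQ-5D | Outcome measures; Data analysis; Cost effectiveness | Sought | Sought |

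Only the first two rows carry an adverse-event or safety label, and only those two are one-sided.

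**Extent of the asymmetry.** Interventions offers up to 10 sessions and expects the pilot's average of eight to be taken up. That is about eight occasions for practitioner logging per acupuncture patient, against none for usual care.

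**Effect on a comparison.** Let p_A and p_C be the true proportions of patients with a non-hospital adverse event. Let a_A and a_C be the chances that the two labelled sources record it.

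- Expected observed difference = a_A·p_A − a_C·p_C.
- If the true risks are equal (p), this is (a_A − a_C)·p, which is not zero unless a_A = a_C.
- If a_C = 0, as the description implies, it becomes a_A·p_A. That cannot be negative, even if acupuncture lowers the true risk.
- With one identical item, if a_A = a_C = a, it becomes a·(p_A − p_C): diluted, but with the right sign, and zero when there is no effect.

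The article gives none of these quantities, so the result fixes the direction of the bias but not its size.

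**What an identical item would and would not buy.** It removes the built-in difference in how events are found. It does not give good power. With n = 220/2 = 110 per arm (equal arms and no loss assumed) and a two-sided 5% test:

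power = Φ{[|p1 − p2| − 1.96·√(2p̄(1 − p̄)/n)] / √(p1(1 − p1)/n + p2(1 − p2)/n)}, where p̄ = (p1 + p2)/2.

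For assumed rates of 5% and 10%, p̄ = 0.075. The numerator is 0.05 − 1.96 × 0.0355 = −0.0196 and the denominator is 0.0354, so power = Φ(−0.55) = 29%. For 5% and 15% it is 70%, for 1% and 5% it is 41%, and for 2% and 5% it is 23%. All these rates are assumptions for illustration. The 188 and 220 under Sample size required rest on the IBS SSS and do not change.

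**The case against.** There are four parts to the case against.

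**Both arms do supply data that bear on harm.** This stands. A reader might infer that the usual-care arm yields no harm data, or nothing beyond admissions, and that worsening of IBS would go unseen. The article does not support that. Worsening is what the primary outcome measures, and it is compared by randomised group at three and 12 months. The Non-Colonic Symptom Score, SF-12 and HADS are also compared between groups, and harm that affects health status or service use enters the EQ-5D and resource comparison. What these measures do not do is identify an event. A side effect that leads to no admission, consultation or change in treatment, and moves no score noticeably, is not recorded as one.

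**No between-arm adverse-event comparison is promised.** This also stands. A reader might infer a contradiction with a planned analysis, but there is none. Collecting acupuncture-related events descriptively is consistent with the stated objectives. The weakness lies in the choice of method.

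**The article is condensed.** This stands in part. The questionnaires are not shown and may already hold a neutral item, so it cannot be stated as fact that usual-care patients are never asked about adverse events. The point does not rest on silence alone, however. The article says how adverse events are sought and ties that to acupuncture, whereas it names both groups when it describes collection of usual care and treatments.

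**Recruitment is over.** The Discussion reports 233 patients recruited between November 2008 and June 2009. This limits how far the questionnaire change can reach, but not the change in reporting.

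**Conclusion.** The point holds in a narrow form. The two sources labelled adverse events or safety are specific to acupuncture, and no identical elicitation is described for both arms. Adverse-event rates from those sources should therefore not be compared between arms. Indirect comparison through hospitalisations, resource use and the outcome scores remains possible.

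The consequence is modest. The primary analysis, the sample size and the cost-effectiveness analysis are untouched. What is lost is a like-for-like adverse-event rate, and the size of the resulting bias cannot be worked out from the article. It does not follow that the net balance of benefit and harm cannot be assessed, or that half the patients go unobserved for non-hospital events: the QALY and resource comparison takes in harm that alters health status or service use, whatever it is called.

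This rests on three assumptions: the open-text questions are framed as the article words them; log books are kept only for patients treated by trial acupuncturists; and data listed without an arm restriction are sought in both arms.

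**What to change.** 1. Put one identical adverse-event item in the remaining 3-, 6-, 9- and 12-month postal questionnaires of both arms, or confirm that it is already there. Word it neutrally: it should ask about any new or worse health problem since the last questionnaire, whatever the cause, without mentioning acupuncture.
2. Base any between-arm adverse-event statement on that item plus hospitalisations. Give the difference with a confidence interval, since power for a test would be low.
3. Report log-book and acupuncture open-text events separately, labelled as acupuncture-only and non-comparative.
4. If the item is introduced part-way, start it on the same date in both arms and restrict the comparison to questionnaires that carried it.

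The cost is a slightly longer form and some coding of free-text replies. Questionnaires already sent cannot be changed. If follow-up runs from recruitment, the last entrants (June 2009) reach three months in about September 2009 and 12 months in about June 2010, so how many remain depends on when the change is made. If none remain, steps 2 and 3 still apply, with hospitalisations as the most direct comparative harm measure and only a proxy for serious events. Because participants are unblinded, an identical item does not guarantee equal reporting, but it removes the difference that the method itself creates.
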